### Methods

#### Trial design

The study employs the Standard Protocol Items Recommendations for Interventional Trials (SPIRIT) [40] as the reporting guideline for this protocol and adheres to Consolidated Standards of Reporting Trials (CONSORT) [41] to ensure quality in study planning, implementation, and reporting.

Figure 1 and Table 1 show the study procedure and the setup of the randomised control trial. This is a 3-arm stratified randomised controlled trial, with four groups distributed across two variants of the spiritual meditation condition (Christian and Islamic), MBSR, and a waitlist control condition. Participants will be first stratified into Christian and Muslim samples and then randomly allocated to one of the three conditions. Individuals assigned to the spiritual meditation condition will be further stratified into either a Christian or an Islamic contemplation subgroup within the spiritual meditation condition based on their religious affiliations.

Participants in the spiritual meditation groups and the secular mindfulness group will receive 8-week interventions, commencing with an initial face-to-face meeting, where they will practice the first session of the guided meditation course using the mobile app. Following that, they will continue with daily guided practices lasting approximately 20 min through the app. Assessment will be held at three time points including pre-intervention (T1, baseline), after the 8-week intervention (T2), and three months after the intervention (T3). Participants in the waitlist control group will only attend the assessments at T1 and T2, as due to ethical reasons they will be given the option to start using the Christian or Islamic meditation App after testing at T2.

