## Participants

### Power analysis

This study will recruit non-clinical samples of 144 Christian and 144 Islamic healthy adult participants. An a priori power analysis was conducted using the G*Power software (V.3.1) [42], considering four groups with mixed method repeated measures at three timepoints. The calculation was conducted based on a small effect size of *f*^*2*^ = 0.1, with an alpha value of 0.05, a desired power of β = 0.85. Effect size was set at 0.1 using a conservative approach due to the novel nature of the study to examine the effects of Christian and Islamic contemplation. Calculation was applied to determine the total sample size of 288 participants with (*n* = 72) per group, after adjusting for an estimated dropout rate of 10%.

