### Randomisation and allocation

First, participants will be stratified into Christian and Islamic samples. They will then be randomly assigned to the spiritual meditation (either Christian or Islamic meditation, with religious affiliation restricting allocation to either the Christian or Islamic type of contemplation), MBSR, or waitlist control, utilizing a random number generator produced by a computer and allocated to one of the four groups. To ensure allocation concealment, the allocation process will be carried out by a researcher who is independent of the trial team.

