### Analysis plan

#### Quantitative data

The analyses will follow both intention-to-treat principle and per-protocol principle, requiring a minimum completion of four days of meditation sessions per week over the 8-week intervention period and complete all required assessments. This study will consider a result with a p-value lower than 0.05 as statistically significant. A series of mixed-design Repeated Measures Multivariate Analysis of Variance (RM-MANOVA) will be used to test the mean difference in the outcomes among conditions (Spiritual meditation, mindfulness, and waitlist control groups) across T1, T2 and T3 as well as within participants across all time points (T1, T2 and T3). The specific prosociality variable, measured by Charitable Giving task, will be only compared between groups at T2. When justifiable, missing data will be imputed using multiple imputation of chained equations [68]. 

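### The stated model uses T1 as a repeated outcome rather than as a covariate and leaves out religion, the stratification factor, so it gives up precision that data already collected could supply

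*Protocol article*

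**What the plan says.** - **Randomisation.** Under Randomisation and allocation: "First, participants will be stratified into Christian and Islamic samples". Under Trial design: "Participants will be first stratified into Christian and Muslim samples and then randomly allocated to one of the three conditions". Within the spiritual arm, the programme follows from faith and not from chance, "with religious affiliation restricting allocation to either the Christian or Islamic type of contemplation".
- **Analysis.** The Quantitative data paragraph names a mixed-design RM-MANOVA. Its between-subject levels are given as "among conditions (Spiritual meditation, mindfulness, and waitlist control groups") and its repeated levels are T1, T2 and T3. Religion is not named as a model term there or elsewhere in the article. Charitable Giving is compared between groups at T2 only.
- **Measurement times.** In Table 2, Dictator Game, social value orientation (SVO), forgiveness and empathy are measured at T1 and T2. Charitable Giving is measured at T2 and perspective taking at all three points. The waitlist attends T1 and T2 only (Trial design; Waitlist condition).
- **Sizing.** The Power analysis section states "This study will recruit non-clinical samples of 144 Christian and 144 Islamic healthy adult participants" and describes the calculation as "considering four groups with mixed method repeated measures at three timepoints". It arrives at 288 participants, 72 per group, after allowing for 10% dropout.

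**The concern.** When an outcome has only two time points, the group-by-time test compares mean changes from T1. That test is valid under randomisation, but it effectively fixes the weight on the T1 value at one. Regressing T2 on T1 estimates the weight and is never less precise in large samples. Four of the six primary measures have exactly two time points. So does every comparison with the waitlist, which is the only between-group contrast for which the article states a directional hypothesis.

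Religion matters separately. It is the stratification factor, so the natural analysis includes it. The question is where its absence costs something. Charitable Giving is the obvious place: it has no T1 value to absorb a difference between the religions, and the receiving charity is itself chosen by the participant's religion.

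**Working it through.** **1. The plan's own figure.** I used the within-between interaction of a repeated-measures ANOVA, with lambda = f²·N·m/(1−rho), df1 = (k−1)(m−1) and df2 = (N−k)(m−1). Inputs from the article are k = 4 groups, m = 3 times, alpha 0.05 and power 0.85. The effect size is read as f = 0.1. Assumed software defaults are rho = 0.5 and no sphericity correction. The result is N = 258 (260 with equal groups), and dividing by 0.9 gives 287 to 289. The stated 288 is therefore reproduced. (Taking the printed f² = 0.1 literally gives about 36.) Completers: 288 × 0.9 ≈ 259.

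**2. Group sizes.** Four groups of 72 from strata of 144 require 72/36/36 in each stratum, that is 2:1:1, which the article does not state. Completers are then 144 × 0.9 ≈ 130 spiritual and 72 × 0.9 ≈ 65 waitlist.

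**3. Change score against baseline adjustment, one outcome at T1 and T2.**
- Change-score variance is proportional to 2(1−rho).
- Adjusted variance is proportional to 1−rho².
- The ratio is (1−rho²)/[2(1−rho)] = (1+rho)/2.

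With 1/130 + 1/65 = 0.02308 and a multiplier of 1.960 + 1.036 = 2.996 for 85% power:

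| rho (assumed) | Variance ratio | SE, change | SE, adjusted | Detectable d, change | Detectable d, adjusted |
|---|---|---|---|---|---|
| 0.3 | 0.65 | 0.180 | 0.145 | 0.54 | 0.43 |
| 0.5 | 0.75 | 0.152 | 0.132 | 0.455 | 0.394 |
| 0.7 | 0.85 | 0.118 | 0.108 | 0.35 | 0.33 |

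At rho = 0.5, power at d = 0.4 is Φ(0.4/0.152 − 1.96) = 0.75 for change and Φ(0.4/0.132 − 1.96) = 0.86 adjusted. Under 1:1:1 allocation (about 86 v 86), 2/86 = 0.0233, so the results barely move.

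**4. The overall three-condition test at T1 and T2** (f = 0.1, 259 completers; lambda divided by (1+rho)/2 for the adjusted version):

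| rho | Power, T1 as outcome | Power, T1 and religion as covariates | N incl. dropout for 85% power, T1 as outcome | N incl. dropout, adjusted |
|---|---|---|---|---|
| 0.3 | 0.68 | 0.86 | 429 | 280 |
| 0.5 | 0.825 | 0.92 | 308 | 232 |
| 0.7 | 0.967 | 0.986 | 186 | 159 |

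**5. What omitting religion costs.** I simulated three arms in two strata, with 43 completers per cell and 3,000 runs.
- *Condition-by-time.* A religion gap that is constant over time cancels in the change. The SE is 0.152 with or without religion (rho 0.5). If the gap grows from 0.5 to 0.8 SD between T1 and T2, the SEs are 0.154 without and 0.152 with religion.
- *T2 only, as for Charitable Giving.* With religions half and half, the SE is inflated by √(1 + g²/4) for a gap of g SD. At g = 0.5 the SE is 0.157 against 0.152. At g = 1 it is 0.171 against 0.152, and the rate of rejecting a true null falls to about 0.026, so the test is conservative.
- *T2 adjusted for T1.* Adding religion takes the SE from 0.133 to 0.132 at a 0.5 SD gap and from 0.136 to 0.132 at 1 SD.

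**The case against.** **The stated test is valid.** Under randomisation the group-by-time test is unbiased, so baseline adjustment is a gain in efficiency and not the repair of an error. The gain depends on a correlation that the article does not give, and at 0.7 it is small (power 0.967 to 0.986). The (1+rho)/2 ratio applies to one outcome at two times, not to a joint test of several outcomes or to data that include T3. All of this stands.

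**The article is condensed.** A fuller analysis plan could add religion as a covariate, so its absence here is weak evidence that it will be left out. That also stands. It does not cover T1, whose role as a repeated level is written into the model.

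**Two stronger readings are tempting but not supported.** A reader might infer that ignoring the stratum inflates the standard errors of the main test. Step 5 shows that a stable religion difference cancels there.

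A reader might also infer, from the four-group wording in Trial design ("with four groups distributed across two variants of the spiritual meditation condition") and in the sizing, that Christian meditation is to be set against mixed-religion controls, so that the whole religion difference enters as bias. The analysis section names three conditions and states no such contrast. If one were run at T2 with half-and-half controls, the bias would be half the difference (0.15 SD for an assumed 0.3 SD gap), and a constant gap would cancel in change from T1. What does remain is that sizing counts four groups while the analysis counts three.

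**Programme differences.** No hypothesis contrasts the Christian with the Islamic programme. A condition-by-religion term is therefore a sensible secondary analysis, not a correction.

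**Conclusion.** The point holds as a matter of efficiency. For Dictator Game, SVO, forgiveness and empathy, and for all waitlist contrasts, the stated model has 1/0.65 to 1/0.85 times the variance of a baseline-adjusted one, that is 1.18 to 1.54 times, for rho from 0.7 down to 0.3. At rho = 0.5 the three-condition test at two time points has power 0.825, just under the planned 0.85, and adjustment brings it to 0.92 with the same participants. Omitting religion matters mainly for Charitable Giving, where the cost is modest at a 0.5 SD gap and clearer at 1 SD.

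The pooled comparison of spiritual meditation, MBSR and waitlist is randomised within religion and is unbiased if the allocation ratio is the same in both strata. The figures rest on assumed values for rho, the allocation ratio and the religion gap, none of which the article gives.

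**What to change.** - Analyse T2 by ANCOVA or a mixed model with condition, religion and the outcome's T1 value as terms. Where T3 is collected, include it for the two active conditions only.
- Adjust Charitable Giving for religion.
- Report condition × religion as a secondary analysis of heterogeneity.
- If either spiritual programme is reported separately, compare it only with MBSR and waitlist participants of the same religion.
- State the allocation ratio, and state that the primary grouping is the three randomised conditions.

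The cost is a change of wording before the data are analysed. Religious affiliation is known from eligibility and stratification, and T1 values are already scheduled for every outcome that has one.

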## Adverse events and safety monitor

We have established an expert panel to guide the study’s design and intervention. Additionally, a dedicated study coordinator oversees the logistical and operational aspects of our research. Given that the potential for adverse events linked to meditation practices [67], we will assess this risk by including a self-report measure for adverse events. Participants will be also asked to reflect on their experiences during the practices. To address concerns, participants can consult religious experts from our advisory board regarding any potential adverse effects of the interventions. They will also be encouraged to promptly contact the lead researcher if adverse events occur, as outlined in the participant information sheet.

Participants undergoing the cold pressor task procedures may experience discomfort or pain, inherent to the procedure’s design. They will be informed that they have the option to discontinue the procedure and remove their hand from the cold water at any time. The cold pressor task is a well-established procedure, and unexpected adverse effects related to the cold pressor task procedure are unlikely to occur. Therefore, based on our risk assessment and the low anticipated risk, a formal data monitoring committee and modifications of allocated intervention are considered unnecessary for this study. It is also unlikely that participants will require post-trial care. However, the lead researcher will closely monitor and document any potential adverse events. Participants will be informed of their right to withdraw from the trial at any time without needing to provide a reason.

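### The intention-to-treat analysis rests on a complete-vector RM-MANOVA with optional imputation, so it may become a completers' analysis and can bias the waitlist contrast

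*Protocol article*

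**What the plan says.** Everything on this point stands in the Quantitative data section of the analysis plan, apart from the dropout figure and the withdrawal rule.

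- Population: "The analyses will follow both intention-to-treat principle and per-protocol principle". A practice threshold follows, together with the condition to "complete all required assessments". I read both as defining the per-protocol set, so the intention-to-treat set is meant to be wider.
- Model: "A series of mixed-design Repeated Measures Multivariate Analysis of Variance (RM-MANOVA) will be used to test the mean difference in the outcomes among conditions", over T1, T2 and T3. Charitable Giving is compared at T2 only.
- Missing data: "When justifiable, missing data will be imputed using multiple imputation of chained equations". No criterion is given for when imputation is justifiable, nor any fallback if it is not.
- Expected loss (Power analysis): 288 participants, 72 per group, "after adjusting for an estimated dropout rate of 10" per cent.
- Withdrawal (Adverse events and safety monitor): "Participants will be informed of their right to withdraw from the trial at any time without needing to provide a reason".

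The Trial design section has the waitlist attend T1 and T2 only. The one directional between-arm hypothesis, in Research question and hypotheses, is spiritual meditation against waitlist.

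**The concern.** The stated model does not deliver the stated principle. RM-MANOVA needs a complete outcome vector, so a participant with T1 but no T2 is removed from the test, T1 score included. Imputation would bring that participant back, but the plan makes it optional. Without it, the intention-to-treat analysis loses much of what separates it from the per-protocol analysis, which requires complete assessments by definition.

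The spiritual-versus-waitlist contrast is at stake. Unequal loss is plausible: the active arms are asked for eight weeks of daily 20-minute sessions, while the waitlist only has to return for T2 and then receives the app. If those who leave the active arms also tend to have low (or high) T1 scores, the completers' mean change shifts through regression to the mean, with no treatment effect at all. An undefined condition also leaves room to decide on imputation once the pattern of loss is known, in a trial whose participants and assessors cannot be fully blinded.

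**Working it through.** **1. The plan's own figure.** Take the G*Power repeated-measures within-between interaction with f = 0.1, k = 4 groups, m = 3 timepoints, alpha 0.05 and power 0.85 (the article prints the power as β). The correlation ρ = 0.5 and ε = 1 are assumed, as the article gives neither. Then λ = f²·N·m/(1 − ρ), df1 = (k − 1)(m − 1) = 6 and df2 = (N − k)(m − 1).

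- N = 260: λ = 0.01 × 260 × 3/0.5 = 15.6, df2 = 512, power 0.854.
- With dropout: 260/0.9 = 289, against the stated 288. In reverse, 288 × 0.9 = 259.2, and N = 259 has power 0.853.
- Reading 0.1 literally as f² gives N = 32 (36 after dropout), so the stated figure matches f = 0.1.

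The 288 therefore corresponds to about 259 evaluable participants, with about 29 (288 × 0.10 = 28.8) counted as lost. That agrees with a complete-case analysis, not with one of all 288 randomised.

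**2. Bias of a completers' change contrast, by hand.** These assumptions are not in the article: no true effect; T1 and T2 standard normal with correlation 0.5; 144 spiritual against 72 waitlist (implied by 72 per group over four groups; no ratio is stated); all loss in the 144 + 72 = 216 active participants, so 28.8/216 = 13.3%; those who leave have the lowest values of T1 plus equal-variance noise.

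- Cut-point: Φ(q) = 0.133, so q = −1.11 and φ(q) = 0.215.
- Mean selection score of those who stay: 0.215/0.867 = 0.248.
- Their mean T1: 0.248/√2 = 0.176 SD.
- Their mean change: (0.5 − 1) × 0.176 = −0.088 SD. The waitlist mean change is 0, so the bias is −0.088 SD, or +0.088 SD if high scorers leave.
- Standard error: the variance of change is 2(1 − 0.5) = 1, and 144 × 0.867 = 124.8 stay, so √(1/124.8 + 1/72) = 0.148. Selection trims it to about 0.146.
- Type I error: 0.088/0.146 = 0.60, so Φ(−1.36) + Φ(−2.56) = 0.087 + 0.005 = 0.092.

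**3. Simulation** (4,000 to 6,000 trials per setting, same T1-T2 model and group sizes):

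| Active v waitlist dropout | Depends on | Bias, completers' change | Type I error | Bias after conditioning on T1 |
|---|---|---|---|---|
| 10% v 5% | arm only | 0.00 SD | 5.2% | 0.00 SD |
| 13.4% v 5% | arm and T1 (logistic, slope 1 per SD) | −0.06 SD | 7.6% | 0.00 SD |
| 13.3% v 0% | arm and T1 (ranked) | about ∓0.09 SD | 9 to 10% | 0.003 SD or less |
| 26.7% v 0% (20% overall) | arm and T1 (ranked) | about ∓0.16 SD | 18 to 19% | about 0 |
| 13.3% v 5% | arm and unseen T2 | +0.06 SD | 7.1% | +0.09 SD |
| 13.3% v 0% | arm and lack of improvement | about +0.17 SD | about 23% | about +0.13 SD |

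Rows 1 to 4 show that the bias needs a link to the T1 score, and that a method which conditions on T1 removes it. The last two rows show that such a method does not cure loss that depends on what was never observed.

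**The case against.** The strongest reply is that this is a condensed article. It names a respectable imputation method, and the criterion for using it is ordinary analysis-plan detail that may exist elsewhere. That stands as far as the missing criterion goes. It does not answer the main point: the article itself fixes a model that deletes incomplete cases and makes the only remedy optional. A later definition would repair this wording, not show that it was sound.

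Several stronger readings are tempting and are not supported:

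- That 10% leave before T2. The Power analysis gives an overall rate only, which may include losses at T3.
- That unequal dropout by itself biases the contrast. Loss related to arm alone gave 0.00 SD.
- That 0.09 SD is the expected bias. It places every loss in the active arms and ties leaving to T1. The article supports neither, the direction is unknown, and zero lies within the range. The 20% row doubles the plan's own rate.
- That T3 losses damage the waitlist contrast. The waitlist has no T3, and perspective taking is the only primary measure with one. Measures at T1-T3 are collected online, so T2 laboratory attendance does not enter their vectors: 5% missing at each of T2 and T3 (assumed) would leave 0.95² = 90%, or 195 of 216 active participants.
- That regression to the mean affects Charitable Giving. It is measured at T2 only and has no change score.
- That the team will choose the more favourable result. The text leaves room for this but does not say it.

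Imputation is also not always safer. When loss depends on the unseen T2 score, adjusting for T1 raised the bias from 0.06 to 0.09 SD.

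**Conclusion.** The concern holds in this form: as written, early leavers enter the intention-to-treat RM-MANOVA only if imputation is later judged justifiable; otherwise that analysis is one of completers. About 29 of 288 participants are affected on the plan's own rate, with timing and arm unknown. The consequence for the T1-T2 spiritual-versus-waitlist contrast is possible bias, not demonstrated bias. It ranges from 0 through 0.06 SD (type I error 7.6%) to about 0.09 SD (about 9%) when dropout depends on arm and T1, and it is larger if non-improvers leave. All these sizes rest on the assumed 144 v 72 split, the assumed correlation of 0.5 and the assumed dropout patterns. The plan should be changed because the remedy is cheap and the defect lies in its own wording. The sample size of 288 is not affected.

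**What to change.** For the intention-to-treat analysis, replace complete-vector RM-MANOVA and the conditional imputation sentence with one rule fixed in advance. All randomised participants are analysed in their allocated arm by one of the following:

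- a likelihood-based linear mixed model with T1 among the responses, which keeps every randomised participant with a T1 value; or
- unconditional multiple imputation by chained equations, run by arm, with T1 scores and religion as predictors. App session counts can be added in the active arms only, since the waitlist has none before T2.

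For Charitable Giving, which has no T1 value, use the same imputation with the other T1 measures as predictors.

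Report completers as a sensitivity analysis, together with one delta-shifted imputation, because a missing-at-random method leaves bias when dropout depends on unseen outcomes.

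The cost is revised wording and modest extra programming. No new data, visits or participants are needed. Intervals may be slightly wider than from completers, because imputation uncertainty is included.

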##### Qualitative data

Thematic analysis will be employed to evaluate the data collected from participants’ diaries regarding their reflections on daily practices and meditation experiences shared in the App, following the 6-step analysis process suggested by Braun and Clare [69]. In step 1, researchers will thoroughly read the diaries and meditation experience multiple times to familiarise themselves with and understand the meaning of the content. In step 2, initial codes will be produced from the diaries and the meditation experience, then organised into meaningful groups. In step 3, codes will be organised into overarching themes. In step 4, themes will be reviewed. In step 5, each identified theme will be defined and labelled. Step 6 consists of the final analysis, selection of representative texts for the themes, and analysis write-up. Data processing and analysis will be conducted using the software NVivo [70]. 

